### Sample size and power calculations

Similar community-based intervention studies using change in symptom-based questionnaires, like the Hospital Anxiety and Depression Scale (HADS) [35–37], have used effect sizes of at least 0.4 when testing treatment as usual groups with limited or no active therapeutic elements, as we propose. Assuming an effect size of 0.4 for the primary endpoint (HADS total score at 20 weeks), with 90% power and 5% significance, an intracluster correlation coefficient of 0.05, and a two-sided hypothesis test with 34 health worker catchment area clusters randomised at a 1:1 allocation ratio, and accounting for 20% attrition, we will need 612 participants (i.e. 306 in each arm). This means that we will need on average 18 participants from each of the 34 health worker catchment areas. A pilot study conducted a nearby Union Council found that these recruitment numbers were feasible and achievable [27], and previous research in the same setting identified a high prevalence of mental health problems in women [38].

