### Statistical methods

Data will be analysed using SAS 9.3 and SPSS Version 21. Findings will be reported according to the Consolidated Standards of Reporting Trials (CONSORT) guidelines for cRCTs [56]. Primary analyses will be based on the intention-to-treat population and secondary analyses will be based on the per-protocol population. A linear mixed model will be employed for the primary endpoint analysis. The mixed model will have treatment, visit, interaction between treatment and visit as fixed effects, baseline measurement of HADS as covariate, and cluster and subject as random effects. The mean difference between two treatment arms at each visit, together with its 95% confidence interval (CI), will be derived from the mixed model. Covariate-adjusted mixed model of primary endpoint will also be performed by adding prespecified covariates at baseline into the above model. Missing data will be treated as missing at random in the mixed model analysis and no imputation of primary endpoint will be made. To assess the sensitivity of the result to this assumption, the last observation carried forward strategy will be used to compute missing primary endpoints. Subgroup analysis will be performed on the prespecified covariates.

Continuous secondary outcomes will be analysed in a similar way as the primary endpoint analysis. For the analysis of binary secondary outcomes, a generalised mixed model will be employed with treatment, visit, interaction between treatment and visit as fixed effects, baseline measurement as covariate, and cluster and subject as random effect. The odds ratio between two treatment arms at each visit together with its 95% CI will be derived from the generalised mixed model.

All analyses will be described in detail in the finalised and signed statistical analysis plan before unmasking the study.

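### The primary mixed model, as listed, holds the baseline-HADS slope equal at 7 and 20 weeks; adding a baseline-by-visit term is a minor, nearly free safeguard for the 20-week contrast

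*Protocol article*

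**What the plan says.** The Statistical methods section of the protocol article lists the terms of the primary linear mixed model. They are treatment, visit, "interaction between treatment and visit as fixed effects, baseline measurement of HADS as covariate", with cluster and subject as random effects. Arm differences are to be derived from this model at each visit. Table 1 gives two post-baseline HADS visits, 7 and 20 weeks, and the sample size section fixes the later one as primary: "the primary endpoint (HADS total score at 20 weeks").

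On missing values the same section says "Missing data will be treated as missing at random in the mixed model analysis", with no imputation of the primary endpoint. Last observation carried forward is the sensitivity analysis named for that assumption. Continuous secondary outcomes follow the same approach, and the model for binary outcomes also has a single baseline term. Full detail is left to a statistical analysis plan to be signed before unmasking, which is not at hand.

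**The concern.** Crossing treatment with visit lets the treatment effect differ between 7 and 20 weeks. Entering baseline HADS once does not allow the same for baseline. Its fitted slope is a compromise between the two visits, and if baseline predicts the 7-week score more steeply than the 20-week score, that compromise is too steep at 20 weeks.

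Two consequences follow if the slopes do differ. First, the 20-week score is adjusted by the wrong amount, which adds some noise to the contrast. Second, a likelihood analysis under missing at random is protected only when its mean model is right. If women with high baseline HADS are lost at 20 weeks more often in one arm than in the other, the women observed differ in baseline by arm, and a wrong slope turns part of that difference into an apparent treatment effect. What is at stake is a small distortion of the primary estimate that the stated missing-data assumption does not cover.

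**Working it through.** **1. The plan's own figure.** The inputs come from the sample size section.

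- Effect, power and level: "Assuming an effect size of 0.4 for the primary endpoint (HADS total score at 20 weeks), with 90% power and 5% significance".
- Clustering, as assumed by the planners: "an intracluster correlation coefficient of 0.05".
- Type of test and number of clusters: "two-sided hypothesis test with 34 health worker catchment area clusters randomised at a 1:1 allocation ratio".
- Losses and the resulting total: "accounting for 20% attrition, we will need 612 participants (i.e. 306 in each arm").
- Cluster size that this implies: "on average 18 participants from each of the 34 health worker catchment areas".

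The arithmetic is then:

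- Individually randomised: 2 × (1.960 + 1.282)² / 0.4² = 131.4, so 132 per arm.
- Design effect: 1 + (18 − 1) × 0.05 = 1.85, and 132 × 1.85 = 244.2.
- Attrition: 244.2 / 0.8 = 305.25, so 306 per arm, 612 in total, and 612 / 34 = 18 per cluster.

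The stated size reproduces. With 306 × 0.8 = 244.8 observed per arm, the design standard error is √(2 × 1.85 / 244.8) = 0.123 SD. This is the yardstick below.

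**2. Assumptions not in the article.** Standardised baseline slopes b7 and b20, with HADS having the same SD at each visit; residual correlation ρ = 0.5 between the two visits; 20% missing at 20 weeks in each arm; log-odds of dropout linear in baseline HADS. The bias check leaves out the cluster effect.

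**3. Precision.** With complete data the residual variance at 20 weeks is 1 − b20² with its own slope, and 1 − b20² + ((b7 − b20)/2)² with the common slope.

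| b7 / b20 | Own slope | Common slope | Variance ratio | SE increase |
|---|---|---|---|---|
| 0.5 / 0.35 | 0.8775 | 0.8831 | 1.006 | 0.3% |
| 0.6 / 0.3 | 0.9100 | 0.9325 | 1.025 | 1.2% |

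Simulating 34 clusters of 18 with about 20% missing gave variance ratios of 1.017 and 1.041 for these two cases. Their square roots are 1.008 and 1.020, an SE increase of 0.8% and 2.0%. The two approaches together give roughly 0.3 to 2%.

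**4. Shift in the 20-week contrast.** Let b_c be the fitted common slope and d the PM+ minus control difference in mean baseline among women observed at 20 weeks. If 7-week data are complete,

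shift = [(b20 − b_c) − ρ(b7 − b_c)] × d.

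If the same women miss both visits, the ρ term drops out. A population-level generalised least squares calculation agreed with this formula. Dropout at 20 weeks only:

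| Log-odds per baseline SD (PM+, control) | b7 / b20 | b_c | d | Shift (SD) | Shift / 0.123 |
|---|---|---|---|---|---|
| +0.5, 0 | 0.5 / 0.35 | 0.438 | −0.096 | 0.011 | 0.09 |
| +0.5, 0 | 0.6 / 0.3 | 0.475 | −0.096 | 0.023 | 0.19 |
| +0.3, −0.3 | 0.5 / 0.35 | 0.438 | −0.118 | 0.014 | 0.11 |
| +0.3, −0.3 | 0.6 / 0.3 | 0.475 | −0.118 | 0.028 | 0.23 |
| +0.5, +0.5 | either | – | 0 | 0 | 0 |

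Worked example, fourth row: [(0.3 − 0.475) − 0.5 × (0.6 − 0.475)] × (−0.118) = (−0.175 − 0.0625) × (−0.118) = 0.028.

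REML fits with cluster and subject random intercepts gave 0.013 and 0.024 for the third and fourth rows, and 0.001 (Monte Carlo SE 0.002) when dropout was unrelated to baseline.

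**5. Scale.** 0.01 to 0.03 SD is 2 to 8% of 0.4. A shift of 0.23 SE would move a two-sided 5% test to about 5.6%. The sign follows the dropout pattern: losing more distressed women from PM+ dilutes a benefit, and the reverse exaggerates it.

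**6. Beyond the moderate range.** Slopes 0.6/0.3 with log-odds ±0.5 give about 0.03 to 0.05 SD. Slopes 0.6/0.2 with ±1 give about 0.07 to 0.11 SD. Only that last kind of case would matter for inference.

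**7. With baseline-by-visit added** the calculated shift is zero in every case. In a separate simulation with 400,000 women per scenario it was below 0.01 SD throughout, which is simulation noise.

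**The case against.** The listed model is a standard repeated-measures specification, and the article contradicts itself nowhere on it. Detail goes to an analysis plan that is not shown and may already cross baseline with visit. That stands as a limit. Even so, the article names the fixed effects one by one, and a plan that followed the list would impose the common slope.

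A reader might infer that the mean model is misspecified, that 20-week HADS is over-corrected, or that the primary result will be biased. The article supports none of these. It reports no baseline-to-outcome correlation and no SD by visit. A slope is a correlation multiplied by a ratio of SDs, so even a correlation that fades over time does not prove unequal slopes.

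The bias needs a second condition as well, and the article gives only 20% attrition overall. Sessions in one arm alone make some dependence in PM+ conceivable, but leaving the sessions is not the same as missing the HADS. The assessors are a separate team and the analysis is by intention to treat. Opposite-sign dropout in the two arms has less support still.

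A reader might also conclude that the model wastes precision in a way that matters. A loss of 0.3 to 2% of the standard error does not bear that out, and the REML variance ratios (0.99 to 1.08) were too noisy to establish a loss.

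**Conclusion.** The point holds as a conditional and minor one. The model as listed imposes one baseline slope on both visits. If the slopes differ, the 20-week contrast loses roughly 0.3 to 2% of its standard error. If 20-week dropout also depends on baseline HADS differently by arm, the contrast shifts by about 0.01 to 0.03 SD under missing at random, at most about a quarter of the standard error. If either condition fails, there is no shift.

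These sizes rest on assumed slopes of 0.5/0.35 to 0.6/0.3, equal SDs, a residual correlation of 0.5, 20% missing, and dropout log-odds of 0.5 per baseline SD in PM+ only or ±0.3 in the two arms. Stronger assumptions give more, but the article offers no evidence for them. Under the moderate range, no conclusion about a 0.4 SD effect would plausibly change. The reason to act is that the remedy costs almost nothing and has to be fixed in advance.

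**What to change.** In the analysis plan, before unmasking, list the fixed effects of the primary model as treatment, visit, treatment-by-visit, baseline HADS and baseline HADS-by-visit. Keep the 20-week treatment contrast as primary and leave the random effects as they are.

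Do the same in the models for secondary outcomes measured at both 7 and 20 weeks, continuous or binary, using each outcome's own baseline. For WHODAS, Table 1 shows that this is the screening score.

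The cost is one extra parameter per model and a short phrase in the plan. No new data are needed and N = 612 stays as it is. Adding the term after unmasking would look data-driven, so the timing matters more than the size of the effect.

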#### Secondary outcome measures

Secondary outcomes include depressive disorder measured by the Primary Health Questionnaire [40–42]; post-traumatic stress disorder (PTSD) symptoms measured by the Post-traumatic stress disorder Check List (PCL-5) [43]; levels of social support measured by the Multi-dimensional Scale of Perceived Social Support (MSPSS) [44]; and levels of functioning as assessed by WHODAS [31]. Costs of health care are measured using the Client Service Receipt Inventory (CSRI) [45]. Self-report wellbeing outcomes are assessed using the Psychological Outcomes Profile Instrument (PSYCHLOPS) [46]. Table 1 indicates the time points for administering each instrument.

**Table 1 Tab1:** Assessment instruments and administered time point

Concept (instrument)	Screening	Baseline assessments	7-week assessment	20-week assessment
Depression and anxiety (Primary outcome)		HADS	HADS	HADS
Functioning	WHODAS		WHODAS	WHODAS
Distress – common mental disorder	GHQ-12			
Depressive disorder		PHQ-9	PHQ-9	PHQ-9
Adverse life events				Section 1 of HTQ Life Events Checklist for Pakistan
Symptoms of post-traumatic Stress Disorder		PCL-5	PCL-5	PCL-5
Perceived social support		MSPSS	MSPSS	MSPSS
Cost of health care		CSRI		CSRI
Self-reported wellbeing		PSYCHLOPS	PSYCHLOPS	PSYCHLOPS

*CSRI* Client Service Receipt Inventory, *GHQ* General Health Questionnaire for common mental disorders, *HADS* Hospital Anxiety and Depression Scale, *HTQ* Harvard Trauma Questionnaire, *MSPSS* Multi-dimensional Scale of Perceived Social Support, *PCL* Post-Traumatic Stress Disorder Check List, *PHQ* Patient Health Questionnaire-9, *PSYCHLOPS* Psychological Outcomes Profile Instrument, *WHODAS* WHO Disability Assessment Schedule for functional impairment

Briefly, the Patient Health Questionnaire-9 (PHQ) is a 9-item instrument measuring the likely presence and severity of depressive disorder against the *Diagnostic and Statistical Manual of Mental Disorders, fourth edition* (DMS-IV) [42]. It uses a 4-point Likert scale where symptom severity is rated over the last 2 weeks from not having the symptom at all, to having it nearly every day. The sum of items gives the total score, with a cut-off of ≥10 as the most accurate for detecting depression [47]. The PHQ has been validated in Urdu [40, 41].

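### The one analysis the protocol article ties to missing at random is LOCF, a single fixed no-change scenario that cannot show how much informative dropout would overturn the result

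*Protocol article*

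**What the plan says.** In the protocol article, Statistical methods, the primary analysis is a linear mixed model with treatment, visit and their interaction, baseline HADS as covariate, and random effects for cluster and subject. On missing values it says: "Missing data will be treated as missing at random in the mixed model analysis and no imputation of primary endpoint will be made". The next sentence gives the check on that assumption: "To assess the sensitivity of the result to this assumption, the last observation carried forward strategy will be used to compute missing primary endpoints".

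The covariate-adjusted and per-protocol analyses in the same section are not offered as tests of MAR. The section closes by leaving the detail of all analyses to a SAP to be signed before unmasking.

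Table 1 (Secondary outcome measures) lists HADS at baseline, 7 weeks and 20 weeks: "Depression and anxiety (Primary outcome) HADS HADS HADS". The design assumption is "Assuming an effect size of 0.4 for the primary endpoint (HADS total score at 20 weeks), with 90% power and 5% significance", and the sample size is set "accounting for 20% attrition". Under Masking, participants, LHWs, facilitators and co-facilitators know the allocation; the researchers who collect quantitative outcomes do not.

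**The concern.** A sensitivity analysis for MAR should show what happens to the treatment effect if women who are lost do worse, or better, than the model predicts from their observed scores, and how far this must go before the conclusion changes. LOCF does not do this. It swaps MAR for one other assumption: that HADS stays frozen after the last score seen.

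- For a woman lost after week 7, the score from shortly after the five weekly sessions stands in for week 20. This assumes that benefit neither fades nor grows, which is what a 20-week endpoint is there to find out.
- For a woman lost before week 7, baseline stands in for week 20. Her outcome then equals her own covariate, and she contributes no effect.

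The first can favour PM+ and the second pulls towards no effect, so the net direction depends on when women leave. Agreement or disagreement with the primary result can therefore arise for reasons unrelated to MAR, and agreement may be read as reassurance that it does not give.

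Informative dropout is plausible here. Participants know their arm, so loss may differ by arm. The article also excludes only women who plan to move within 3 months (Participant exclusion criteria), while the endpoint is at 20 weeks, so later planned moves are not screened out.

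**Working it through.** **Inputs from the article (Sample size and power calculations):** standardised effect 0.40; 90% power; two-sided 5%; ICC 0.05; 34 clusters (17 per arm); 18 women per cluster; 20% attrition; 612 in total.

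**Assumptions not in the article:** a week-7 effect of 0.6 SD; the timing of dropout; equal dropout in both arms; the size of any shift in unseen scores. Effects are control minus PM+, so positive values favour PM+.

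**1. The plan's own figure.** Individually randomised n per arm = 2 × (1.96 + 1.282)² / 0.40² = 131.4, so 132. Design effect = 1 + (18 − 1) × 0.05 = 1.85. Then 132 × 1.85 = 244.2, and 244.2 / 0.8 = 305.25 per arm. Since 17 × 18 = 306, the total is 612. The stated size reproduces.

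**2. LOCF when MAR holds exactly.** Let f be the share of dropouts who have a week-7 score and e7 the week-7 effect. Those carried from baseline contribute zero on average, so

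LOCF estimate = 0.8 × 0.40 + 0.2 × f × e7.

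| Dropout timing | e7 (assumed) | LOCF estimate | Change from 0.40 |
|---|---|---|---|
| All before week 7 (f = 0) | any | 0.32 | −20% |
| Half and half (f = 0.5) | 0.5 | 0.37 | −7.5% |
| All after week 7 (f = 1) | 0.6 | 0.44 | +10% |
| All after week 7 (f = 1) | 0.8 | 0.48 | +20% |

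Nothing informative has happened in any row. The method alone moves the estimate.

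**3. LOCF when dropout is informative.** In a large-sample simulation of the half-and-half row, the unseen week-20 scores of PM+ dropouts were worsened by 0, 0.5, 1.0 and 1.5 SD. The true effect fell to 0.40, 0.30, 0.20 and 0.10, while LOCF stayed at 0.37. No analysis of observed data alone can react to unseen scores, so this is not peculiar to LOCF. It shows why the departure has to be an explicit input that can be varied, and LOCF offers none.

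**4. Standard error.** SE = √(2 × (1 + (m − 1) × 0.05) / (17 × m)). At m = 18, with filled values counted as observed, it is 0.110. At m = 18 × 0.8 = 14.4, respondents only, it is 0.117. The apparent gain is about 6%, but that treats the mixed model as a respondents-only analysis. The model also uses week-7 scores. If every dropout has one and its correlation with week 20 is 0.6 (assumed), the model's SE is about 0.114 and the gain about 4%.

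**5. What a delta analysis would show.** If PM+ dropouts are worse than MAR predicts by δ (in SD), the estimate is the observed effect minus (share missing × δ). Holding the SE at its respondents-only value, with 20% missing and an observed effect of 0.40:

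- δ = 0.25: 0.35, z = 3.0
- δ = 0.5: 0.30, z = 2.6
- δ = 1.0: 0.20, z = 1.7

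Tipping point = (observed effect − 1.96 × SE) / share missing:

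- observed 0.40, 20% missing: (0.40 − 1.96 × 0.1168) / 0.2 = 0.86 SD
- observed 0.30, 20% missing: (0.30 − 1.96 × 0.1168) / 0.2 = 0.36 SD
- observed 0.40, 10% missing: (0.40 − 1.96 × 0.1131) / 0.1 = 1.78 SD
- observed 0.40, 30% missing: (0.40 − 1.96 × 0.1215) / 0.3 = 0.54 SD

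The same δ in both arms with equal dropout cancels and leaves 0.40, so shifts must be able to differ by arm.

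**The case against.** Four points can fairly be made for the plan.

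- **LOCF is a non-MAR scenario.** It does embody one alternative, no change after the last score, so it is not uninformative. This stands. The criticism is that it is one scenario that cannot be graded or varied by arm.
- **The article is condensed.** The signed SAP may add other analyses. This also stands: a reader might infer that the trial has no other check on MAR, but the article supports that only for its own text. It does not excuse the choice of LOCF, which the article states as the method.
- **The primary analysis is sound.** "Missing data will be treated as missing at random in the mixed model analysis", and the model uses baseline HADS and both follow-up visits. A reader might infer from the 0.32 to 0.44 SD range that the trial's result will be biased by that amount. It will not: the range concerns a supporting analysis. Nor does the statement that the primary endpoint is not imputed contradict the use of LOCF, since it describes the mixed model.
- **The conclusion is fairly robust at the design values.** LOCF estimates of 0.32 and 0.44 over an SE of 0.110 give z of about 2.9 and 4.0, against 0.40 / 0.117 = 3.4 under MAR. PM+ dropouts alone would have to be about 0.86 SD worse than predicted before significance is lost. So it is not shown that informative dropout would overturn a result of 0.40 SD; the point bites with a smaller effect or higher attrition. The 20% is also a planning allowance, not a forecast.

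A reader might also call the trial unmasked. It is single-blind: outcome assessors are masked and give HADS first. Knowledge of allocation among participants, LHWs and facilitators bears on who stays, not on masked assessment.

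**Conclusion.** The point holds as a weakness in a stated sensitivity analysis, not as a flaw in the primary analysis. LOCF is a poor instrument for the purpose the article gives it. It fixes one no-change scenario, counts filled values as data, and leaves the reader unable to tell how strong informative dropout would need to be.

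Under the assumed timing and an assumed week-7 effect of 0.6 SD, it returns 0.32 to 0.44 SD where the truth is 0.40 SD and MAR holds. The more useful quantity is the tipping point. It moves from about 0.86 SD to about 0.36 SD as the observed effect drops from 0.40 to 0.30 with 20% missing, and LOCF reveals neither figure. These tipping points assume equal dropout in both arms, a shift in PM+ dropouts only, and an SE unchanged by the imputation. The change should be made before the SAP is signed.

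**What to change.** Keep the mixed model as the primary analysis. Replace LOCF as the check on MAR, or demote it to a supplement, as follows:

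1. Multiply impute week-20 HADS under MAR separately by arm, using baseline and week-7 HADS and an imputation model that respects the LHW clusters.
2. Add delta shifts to the imputed values in the PM+ arm alone, and then with separate values for each arm.
3. Prespecify the grid and make it wide enough to reach the tipping point: at least 0 to 1 SD at the planned 20% attrition, and wider if attrition is lower (about 1.8 SD at 10%). A grid that stops at 0.5 SD would not reach it at the design effect. State the shifts in HADS points as well; the article gives no SD for the conversion.
4. Report the estimate and 95% CI across the grid and the tipping point, with dropout by arm and by visit.

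The cost is SAP text and modest programming. No data collection changes. The article says that the SAP is to be signed before unmasking and that recruitment was still under way when it was submitted.

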#### Economic analysis

Health economic analysis will be conducted to determine the difference in costs and outcomes in the intervention arm as compared to the control arm.

We take a broad public health and societal perspective to assessing economic implications, including all direct cost of health, social, voluntary and private sector services accessed by participants; productivity losses of the participant and caregivers; and informal care and out-of-pocket expenses.

Primary analysis will be of total costs over the 20-week follow-up treatment period. Recognising that cost data are often skewed, the bootstrap technique will be applied. The sampling with replacement from the original observed paired of costs and effects will be employed to maintain the correlation structure between costs and benefits, and bootstrapping sampling will be repeated 1000 times. For each bootstrap sample, an estimate of differential total mean costs and expected mean effectiveness will be calculated. The 95% CIs for the differential estimates will be derived from the 2.5th and 97.5th percentiles [57, 58].

Cost-effectiveness will be assessed by combining costs with the outcome measures including (1) HADS-A and HADS-D scores and (2) WHODAS total score in incremental cost-effectiveness analysis. Repeat resampling from the costs and effectiveness data (bootstrapping) will be used to calculate the probability that each of the treatments is the optimal choice, subject to a range of possible maximum values (ceiling ratio) that a decision-maker might be willing to pay for a unit improvement in HADS-A and HADS-D scores, and WHODAS scores.

The results of the cost-effectiveness will be reported as incremental cost-effectiveness ratios, and acceptability curves which summarise the information contained in a cost-effectiveness plane [59].

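### The economic bootstrap, as written, has no cluster level, so its intervals and acceptability curves overstate certainty if costs or effects correlate within Lady Health Worker (LHW) areas

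*Protocol article*

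**What the plan says.** The Economic analysis section of the protocol article names what is resampled and why: "The sampling with replacement from the original observed paired of costs and effects will be employed to maintain the correlation structure" linking costs to benefits. It adds that "bootstrapping sampling will be repeated 1000 times" and that "The 95% CIs for the differential estimates will be derived from the 2.5th and 97.5th percentiles". The acceptability curves come from the same kind of procedure: "Repeat resampling from the costs and effectiveness data (bootstrapping) will be used to calculate the probability that each of the treatments is the optimal choice". The section mentions no cluster, no two-stage resampling and no multilevel model.

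Elsewhere the article treats clustering as part of the design. Under Randomisation, 34 LHW clusters are allocated 1:1. The Sample size and power calculations section assumes "an intracluster correlation coefficient of 0.05". Under Statistical methods, the primary mixed model has "cluster and subject as random effects", and the models for secondary outcomes follow the same pattern.

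**The concern.** A cost-effect pair exists for each participant, so drawing pairs with replacement means drawing women as if they were independent. That preserves the correlation between a woman's cost and her outcome, which is the only purpose the section gives. It does not preserve the correlation between women in the same LHW area. In a cluster trial the second correlation is the one that inflates the variance of a difference between arms.

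Cost-effectiveness is one of the trial's objectives, and lower health costs at 20 weeks is a secondary hypothesis (Objectives and hypothesis). The HADS subscales would be analysed with a cluster effect in the clinical report and without one in the economic report, so the same women's scores would carry two different levels of uncertainty. The acceptability curve, which a decision-maker would read most directly, would look more certain than 17 randomised units per arm support.

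**Working it through.** **Inputs.** From Sample size and power calculations: effect size 0.4, 90% power, two-sided 5%, ICC 0.05 (HADS total), 34 clusters, 18 women per cluster, 20% attrition, 612 in total. From Economic analysis: 1000 resamples and percentile intervals. Derived: 17 clusters per arm; 18 × 0.80 = 14.4 analysed per cluster. Assumed: an ICC of 0.01 to 0.10 for cost or net benefit, since none is given.

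**1. The plan's own figure.** Two means at 0.4 SD need 132 per arm. The design effect is DE = 1 + (18 − 1) × 0.05 = 1.85. Then 132 × 1.85 = 244.2, and 244.2 / 0.80 = 305.25, so 306 per arm and 612 in total, as stated. Without clustering, 132 / 0.80 = 165 per arm, or 330 in total. The design therefore pays heavily for clustering.

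**2. Effect of leaving clusters out.** The true SE is √DE times the SE that treats women as independent. Coverage of the nominal 95% interval is 2Φ(1.96/√DE) − 1.

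| ICC | Women per cluster | DE | √DE | Coverage |
|---|---|---|---|---|
| 0.01 | 14.4 | 1.134 | 1.065 | 93.4% |
| 0.02 | 14.4 | 1.268 | 1.126 | 91.8% |
| 0.05 | 14.4 | 1.67 | 1.292 | 87.1% |
| 0.05 | 18 | 1.85 | 1.360 | 85.0% |
| 0.10 | 14.4 | 2.34 | 1.530 | 80.0% |

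At ICC 0.05 and 14.4 per cluster, the reported SE is 1/1.292 = 0.77 of the true one, about 23% too small.

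**3. Acceptability curve** (normal approximation for net benefit, 14.4 per cluster). A stated 0.95 becomes Φ(1.645/1.292) = 0.898, and a stated 0.90 becomes 0.839. For ICC 0.01 to 0.10, the 0.95 becomes 0.939 to 0.859.

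**4. Simulation.** 17 clusters of 14 per arm, 500 trials, 1000 resamples, percentile intervals. The lognormal ICC is set on the log scale. The width ratio is cluster interval over individual interval.

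| ICC | Data | Individual pairs | Whole clusters | Width ratio |
|---|---|---|---|---|
| 0 | normal | 95.2% | 92.4% | 0.95 |
| 0 | lognormal | 94.0% | 93.0% | 0.96 |
| 0.01 | normal | 92.2% | 92.6% | 1.02 |
| 0.01 | lognormal | 91.4% | 91.2% | 1.01 |
| 0.05 | normal | 86.4% | 94.0% | 1.24 |
| 0.05 | lognormal | 87.8% | 93.0% | 1.14 |
| 0.10 | normal | 80.8% | 93.4% | 1.46 |
| 0.10 | lognormal | 85.2% | 92.4% | 1.28 |

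Simulation error is about √(0.87 × 0.13 / 500) = 1.5 percentage points at 87% coverage.

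The loss is milder in the lognormal rows at 0.05 and 0.10. Much of this is a matter of scale. With unit variance on the log scale, a log-scale ICC of 0.05 is (e^0.05 − 1)/(e − 1) = 0.030 on the cost scale. Then √(1 + 13 × 0.030) = 1.18, and the plain cluster bootstrap shrinks this by about √(16/17) = 0.970 to 1.14, which matches the table. The same shrinkage explains why whole-cluster resampling still falls slightly short of 95%.

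**The case against.** **The article does not say that women are resampled regardless of cluster.** This is true: the individual level is a reading, and intact pairs are compatible with resampling clusters. But it is the plain reading, because the section states a scheme, gives its purpose, and includes no cluster step.

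**The detail may be in the SAP.** Statistical methods defers detail to a signed analysis plan and commits to CONSORT reporting for cluster trials, so the SAP may already have a cluster level. The article does more than stay silent, however. It fixes a resampling scheme and says that the intervals come from it. If the SAP differs, the published text still needs correcting.

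**Secondary outcomes follow the primary mixed model.** Costs and cost-effectiveness have their own method and their own source of intervals, so that general sentence does not reach them.

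**No cost ICC is given.** This stands. The 0.05 is a planning value for HADS total. Some positive clustering of cost is plausible, since women in an area share one LHW and the groups meet in her house. But productivity losses, informal care and out-of-pocket spending need not cluster by LHW. At ICC 0.01 the two bootstraps are practically indistinguishable in the simulation.

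**Stronger readings that the article does not support.** A reader might infer that the cost intervals are certainly too narrow, or that cost clusters more strongly than HADS. The article gives no figure for either. A reader might also turn 87% coverage into a 13% type I error for a cost test. The section names no such test, and the conversion holds only if an interval excluding zero is used as one.

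**Conclusion.** The point holds conditionally. Followed as written, the economic bootstrap omits a source of variation that the rest of the design treats as material. If costs or effects are positively correlated within LHW areas, its intervals are too narrow and its acceptability probabilities too extreme.

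For the HADS effects, the plan's own ICC implies coverage of about 87% (86% to 88% in simulation) at 14.4 per cluster. For costs and net benefit the size is an assumption: about 93% to 80% over ICC 0.01 to 0.10 by the normal formula, and less severe in the skewed simulation at the upper end.

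It would be wrong to infer that the trial's main result is compromised. The primary HADS model includes clusters, and the bootstrap level does not bias the cost difference, the effect difference or the incremental cost-effectiveness ratio. No probability or willingness-to-pay threshold is set, so moving from 0.95 to about 0.90 crosses no prespecified decision rule. This should be fixed before unmasking, but it does not put the trial's validity at risk.

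**What to change.** State the resampling level in the Economic analysis section and in the SAP. Either of these would serve:

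- Resample LHW clusters with replacement within arm, keep each woman's cost-effect pair intact, and apply a small-cluster correction (for example, a two-stage bootstrap with shrinkage). A plain cluster percentile bootstrap with 17 clusters per arm covered only 91% to 94% in the simulation.
- Fit a bivariate model of costs and effects, or a net-benefit mixed model, with a cluster random effect.

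Use the chosen method throughout: for the cost and effect differences, the uncertainty around the incremental cost-effectiveness ratio, and the acceptability curves. If the SAP already does this, only the article's description needs correcting.

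No new data are needed. The cost is some extra programming and wider intervals: about 1.29 times as wide at ICC 0.05 and 14.4 per cluster, and 1.06 to 1.53 times over the assumed ICC range.
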